## Abstract

Football (soccer) is a very popular team sport among African women and girls, with player numbers continuing to rise at all levels of the sport. Whereas the participation in football and associated injuries are on the rise, there are not enough sports and exercise medicine (SEM) personnel to attend to these women football players. While Africa may not currently have enough SEM trained medical doctors and/or physiotherapists, it has relatively higher numbers of other healthcare workers; for example, nurses, who lead healthcare services provision from community to tertiary levels. The primary objective of this study will be to compare sports medicine practices; injury prevention behaviours; injury risk parameters; incidence and prevalence of injuries and illnesses in teams with and without a Football Nurse during one competitive season in Malawi’s Women’s football league. This study will be a cluster randomised control trial will recruit 24 teams from the Women’s Football League in Malawi, which will be randomised to either the intervention group or the control group. A cohort of 12 nurses will receive training in basic football medicine; after which they will be attached to a total of 12 women’s football teams (intervention group) during one competitive season. The Football Nurses will be directly report to a physiotherapist or doctor in their district to whom they will refer serious injuries for investigations, or further management. The teams with Football Nurses will be compared to other teams that will not have Football Nurses. We expect to develop a low cost, sustainable and context relevant solution to manage the treatment gap of football injuries/illnesses in underserved communities such as women’s football.

**Trial registration number:** Pan African Clinical Trial Registry (PACTR202205481965514).

## Introduction

### Women’s football

Football (soccer) is a very popular sport among women and girls in Africa and the numbers continue to rise at all levels of the sport [1, 2]. The world football governing body has shown its commitment to improving the women’s game by providing $ 1 billion in funding to the Women’s Football Development Department [3]. Similarly, national associations are also investing more in their women’s teams and more commercial sponsors such as celebrities are coming on board to sponsor women’s football [4]. Further, the recently concluded WEURO and AWCON Championships broke attendance and viewership records [5, 6], which shows the growing interest in women’s football as a spectator sport.

This increase in participation and professionalisation of the women’s game is also directly associated with an increase in football related injuries [7–9]. Typical football injuries/adverse events include ligament sprains, muscle strains, or concussions [8, 10]. However, while the tide in women’s football is turning towards a more professional approach in the Global North, the same cannot be said about progress in the Global South or at grassroots level, where resources, human or otherwise, continue to be scarce. Hence, while the physiology of football injuries may be the same, injuries and illnesses in women’s football players in low- and middle- income countries (LMICs) such as in sub-Saharan Africa (SSA) have different socioeconomic implications for management and return to play to those faced by their counterparts in high income countries (HIC). This is, in part, because trained medical care is very limited in the former [11–14] compared to the latter [15].

Recent studies on African sport have shown that more than 50% of athletes do not have medical attendees at training or competition [12, 13, 16]. These findings may be attributed to the shortage of trained sports and exercise medicine (SEM) practitioners such as medical doctors (hereinafter referred to as doctors) and/or physiotherapists (PTs) in SSA. In such an environment of scarcity, it is the women, children and those with disabilities who bear the brunt of these shortages [17] and SEM is no different: medical care is very limited for women’s, youth, and para football teams worldwide [18]. It is widely believed that available and suitably trained SEM personnel would sooner practice with a (adult) men’s team where the benefits and conditions of service are more lucrative.

When women’s teams do have medical cover, it tends to be variable with no continuity of practice and care, and players may need to pay for themselves [18]. Consequently, women players may suffer worse outcomes from injury because they are at the periphery of health services provision in football [19], which compromises their safe participation in the sport [20, 21]. SEM is a relatively new discipline in Africa, therefore the number of specialists is proportionately less than other established disciplines of medicine [12, 14]. Hence, while participation in football and injuries arising thereof are increasing, there are not enough SEM specialists to attend to these football players, which results in an enormous treatment gap in sports injuries. Consequently, 70% of injured athletes do not receive medical treatment or specialist referral following injury on the field of play [11].

### Nurses as health care providers in LMICs

A solution to this shortage of trained SEM professionals and subsequent treatment gap in women’s football, proposed by the investigators, is to train more professionals. However, therein lies another challenge: there are currently not enough institutions that train doctors and/or PTs on the African continent to meet the basic health needs of their populations, let alone ‘spare’ for sport **(Table 1)**.The current medical best practice in football requires to have at least a doctor, PT and conditioning coach at the pitch side during training and matches [21–23]. This best practice model is based on personnel availability in HIC **(Table 1).** Therefore, it may seem impossible to achieve in most teams in LMICs. As a result, most football teams in Africa, especially women’s teams, have to do without medical care at training or practice except perhaps at national team level.

**Table 1 pone.0278428.t001:** The number of institutions that train medical doctors and physiotherapists in three selected low-income African countries (Zimbabwe, Uganda, and Malawi) compared to those trained in a high-income country (Australia).

Country	Population (million)	Doctor training institutions (approx. number of graduates per year)	PT training institutions (approx. number of graduates per year)
**Zimbabwe**	14.7	3 (200)^a^	1 (25)^a^
**Uganda**	44.3	6 (400)^b^	2 (20)^b^
**Malawi**	18.6	1 (80)^c^	1 (25)^c^
**Australia**	25.7	22 (3600) [24]	24 (2500)^d^

^**a**^[name], 2021

^**b**^[name], 2021

^**c**^[name], 2021

^**d**^[name], 2021

While SSA may not currently have enough doctors and PTs, SSA also tends to have relatively higher numbers of other health workers; namely, nurses [25]. For example, Zimbabwe has 0.24 PTs; 1.6 doctors and 7.2 nurses to 10 000 citizens [26, 27] and close to 80% of all healthcare workers in South Africa are nurses [25]. Consequently, the bedrock of health systems in SSA is nurse-led. This heavy reliance on nurses as the main healthcare providers is reflected in the number of nursing schools and graduates in SSA. Zimbabwe and Uganda have 27 [28] and 50 institutions *([name]*, *2021; personal communication)*, respectively, that train nurses while Malawi graduates approximately 2000 nurses annually *([name]*, *2021; personal communication)*.

In the pyramidal referral system used in many LMICs, doctors are available from secondary health care (e.g. district hospital) and PTs are often available from tertiary health care (e.g. provincial hospital) while nurses are available from the community and primary care levels and throughout the referral pyramid [25, 29]. Hence, while access to a doctor or PT may be aspirational for most citizens/athletes of SSA, discretionary even, nurses are available to provide healthcare from grassroots level and sometimes healthcare facilities are exclusively staffed by nurses [25, 30]. A mirror strategy of having nurses available to provide health care from the community and primary care levels with doctors and PTs available at higher levels may be used in football medicine to ensure that health care services are provided for all participants at all levels of the game, especially at grassroots.

### Inclusion of nurses in task sharing in SEM

Perhaps, instead of having an SEM strategy that is heavily reliant on doctors and PTs as in HIC, we ought to adapt current global standards to fit the human resources profile of SSA and include the largest group of healthcare providers by numbers, nurses. In general medical practice, nurses currently conduct screening, diagnosis and management of medical conditions as well as referring to other healthcare workers as necessary and are an integral part of healthcare delivery in most LMICs [25, 30]. Similarly, they should be a key component to delivering health care services in football especially at grassroots levels and for underserved football players. Including nurses in the SEM practice agenda may help alleviate the shortage of pitch side medical care in women’s football teams. Additionally, as nurses are predominantly women [31], their inclusion into SEM practice will also help increase representation of African women SEM practitioners as they are still underrepresented in the profession [32].

Therefore, the aim of this project is to develop a task sharing approach (Football Nurse) to actively recruit and train nurses as pitch side responders in grassroots women’s football. Similar task sharing approaches have been used successfully in other sporting codes [33] and in LMICs to manage the diagnosis, treatment, and referral of other health conditions where there is a shortage of specialists [30]. The broad aim of this project is to explore the influence of trained nurses as pitch side responders in grassroots women’s football teams. Therefore, to minimise contamination, the unit of randomisation and analysis will be the football team.

### Rationale for components of the task sharing approach

Globally, women and girls in sports are confronted with the lack of gender friendly sports facilities, equipment, and support personnel [11]. While these barriers to safe participation of women in sport are widely acknowledged, there is a dearth of follow up interventions to specifically address these barriers. Despite an increase in participation in football, most women’s football teams in Africa do not have medical care at training or during competition [11]. This is likely because there are not enough doctors and/or PTs to service these teams. The problem with the status quo is that this inadequate access to sports medical services increases the risk of injury, worsening of injury once incurred, or reinjury [13, 20, 21]. Hence, it is imperative that this gap be filled to ensure safe participation of women players in the game.

Nurses are the largest number of healthcare workers by numbers and are the backbone of most health systems in LMICs. Actively including nurses into SEM practice in these settings may provide an effective, affordable, and sustainable solution to bridge the treatment gap that African women football players currently face and allow safer participation in football activities for all, at all levels. The goal of the FIFA Football Nurse project will be to use a task sharing approach to train nurses to provide on field assessment and management of sports injuries in underserved communities such as grassroots women’s football. This will ensure that the SEM needs of women football players are met from grassroots level.

## Research aim and hypotheses

The overall objective of the FIFA Football Nurse project will be to train nurses as first responders in grassroots women’s football. The main aim of the project is to use the rigour of a randomised control trial (RCT) to evaluate the influence of trained nurses as first responders on sports injury related outcomes following Football Nurse intervention compared to usual treatment in grassroots women’s football teams. The main outcomes will be at level of the team SEM practice (women’s football teams are the clusters). We hypothesise that the FIFA Football Nurse intervention will be superior to the current management in grassroots women’s football teams. Lastly, the project will evaluate the feasibility of training nurses as first responders in grassroots women’s football teams.

### Specific objectives

#### Primary objective

To estimate the effect of football nurse intervention on team sports medicine practice during one competitive season in Malawi’s Women’s football league.

#### Secondary objectives

Determine current sports medicine practices in women’s football teams in Malawi’s Women’s Football League.Determine baseline knowledge, attitudes, and behaviours of football stakeholders (players, coaches, team management) in women’s football towards injury prevention programs in teams with and without a Football Nurse during one competitive season in Malawi’s Women’s football league.Identify football injury risk factors among women’s football players in teams with and without a Football Nurse during one competitive season in Malawi’s Women’s football league.Determine the incidence and prevalence of injuries, illnesses, and medication use in teams with and without a Football Nurse during one competitive season in Malawi’s Women’s football league.Determine treatment and referral protocols of injuries and illnesses in teams with and without a Football Nurse during one competitive season in Malawi’s Women’s football league.To determine the financial feasibility of the FIFA Football Nurse intervention in grassroots women’s football in Malawi.

We hypothesise that compared to teams without a Football Nurse, the mean sports medicine practice will be higher among teams with a Football Nurse during one competitive season in Malawi’s Women’s football league.

## Materials and methods

### Football nurse intervention

The purpose of this study will be to evaluate the effect on teams’ sports medicine practice of randomising women’s football teams to a trained general nurse as a pitch side responder or usual practice. This study will be a cluster randomised control trial, whose reporting will follow the Consolidated Standards of Reporting Trials (CONSORT) 2010 statement: extension to cluster randomised trials [34]. Clusters will be registered teams in the Women’s Football League (24 teams) in Malawi. A 1x1 factorial design will be used to assess the effect of the FIFA Football Nurse intervention. The two allocated groups will be the football teams’ (clusters) sport medicine practice. The teams will be randomly assigned to intervention or control. Prior to the commencement of the intervention, a survey will be sent out to the women’s football teams to explore the current state of healthcare provision and policies for management or referral of players with injuries or illnesses, knowledge of injury prevention programs as well as their present medical needs. Following this, a cohort of 12 general nurses will receive a one (1) day training in basic football medicine using the latest version of the FIFA Emergency Care training manual. This training will be conducted by experienced sports medicine personnel as well as experienced trainers in basic life support (BLS) and first aid from the Departments of Emergency and Orthopaedics at Kamuzu University of Health Science (KUHeS), Blantyre, Malawi. Following the training, the nurses will be attached to a total of 12 women’s football teams during one competitive season. They will also be given access to reference materials that are adapted from the FIFA Emergency Care manual.

The roles of the nurses within the teams will include menstrual, basic health, injury risk assessment, nutritional, and mental health assessment; on field assessment, basic life support; immediate care, and referral of injuries; as well as maintaining records of injuries, illnesses, medication use and football exposure using standardised instruments as previously used in other studies [35, 36].

The trained nurses will be directly supervised by and report to a physiotherapist or doctor within their district **(Fig 1)** to whom they will refer players for intermediate care [11], refer serious injuries, refer players for investigations, or further management. The selected teams and nurses will be followed up for one season and outcomes measured at specified time points during the season as shown in **Fig 1.** Additionally, at the end of the season, semi- structured interviews will be conducted with the a selected sample of women football players and coaches from both arms of the study, as well as all nurses. The aim of these interviews will be to conduct an in- depth exploration of the participants’ lived experiences and perceptions of the football nurse task sharing approach.

**Fig 1 pone.0278428.g001:**
[figure not shown]
Proposed referral pathways for players with injuries or illnesses during the FIFA football nurse intervention.

Current team medical practice; knowledge and practice of injury prevention strategies, injury risk; and mental health assessment will be assessed at the beginning, halfway through and at the end of the season. Football exposure; injuries, illnesses, and medication use surveillance will be recorded after every training session or match event throughout the season.

### Trial design and study arms

#### Trial design

This study will be a cluster randomised controlled trial. This design is applicable as it allows for a field-based intervention to be implemented for one competitive season while decreasing the chances of contamination between the groups. African women’s football is the sport that has been chosen as it is the most commonly played women’s team sport on the continent and therefore, is a priority sport for improving medical care at and from grassroots levels. Adherence to the FIFA Football Nurse program; football exposure data; injury, illness and medication use surveillance and the in this trial will be similar to those used in previous football studies [35, 37] and conform with the definitions and data collection procedures outlined in the latest injury consensus statements [36]. The study will also include a qualitative evaluation of the participants’ (players, coaches, nurses) experience of the FIFA football nurse program.

All the 24 women’s teams in the Malawi Women’s Super league will be randomly assigned in a 1:1 ratio to either the Football Nurse intervention (INT–12 teams) or the control group/standard care (CON–12 teams) through a random draw. For the allocation schedule for random assignment to each arm, the names of the 24 teams will be placed in three (3) bowls, a bowl for each region. They will then be picked consecutively and alternately, and allocated into the INT and CON groups by one of the investigators ([name]). This will be done after the training of the nurses and after each team (cluster) have agreed to be a part of the study. For transparency, the random draw will be conducted in the presence of representatives from the football association and will be video and audio- recorded.

#### Control or standard care

In the control or standard care group (CON) consisting of 12 teams (clusters), each team will have 30 registered players, one (1) team manager, and one (1) coach and will continue their SEM practise ‘as per usual’. A member of the research team will contact a designated member of their technical personnel to collect data on football exposure; injury, illness and medication use surveillance after each training session and league match. Beyond this, the teams in the CON group will not receive any special instructions. It is noteworthy that the teams in the CON and INT groups will at some point in the season play against each other and the Football Nurse will be duty bound to render care should a player from the CON group be injured or fall ill during the match. Therefore, contamination cannot be entirely avoided.

#### Football nurse intervention

In the intervention group consisting of 12 teams (clusters), each team will have 30 registered players, one (1) team manager, and one (1) coach. Each team in the intervention group will be have one (1) trained general nurse assigned to them for training and match cover for the duration of one competitive season. The nurses will be supervised by and directly report to a physiotherapist or medical doctor to whom they will refer serious injuries, investigations and further management/rehabilitation as needed.

#### Sample size

The study aims to evaluate the impact of the Football nurse intervention on team sports medicine practice. Hence, the study will recruit twelve (12) nurses, with one assigned to each intervention team, and six (6) physiotherapists and/or doctors to supervise the Football Nurses from two teams each.

To determine the appropriate sample size, the study used the cluster randomized formula as in previous studies [38]. This formula considers the intra-cluster correlation coefficient, number of participants, expected effect size, and power of the study. The formula is as follows:

$$C=1+{\left(Z_{\alpha /2}+Z_{\beta }\right)}^{2}\frac{\left[\sigma_{0}^{2}+\sigma_{1}^{2}\right]\times [1+(m-1)k]}{m{\left(\mu_{0}-\mu_{1}\right)}^{2}}$$

Where C is the number of clusters required per treatment arm, *Z*_*α*/2_ and *Z*_*β*_ are the critical values of the standard normal distribution for the desired confidence level and power, respectively, *m* is the number of individuals per cluster and *k* is the intracluster coefficient, *μ*_1_ and *μ*_0_ are the true means, and σ_1_ and σ_0_ are the standard deviations, of the outcome variable in the presence and absence of the intervention, respectively.

The design effect of a CRT is related to the intracluster correlation coefficient as follows:

DEFF=1+(m−1)k

Assuming a 95% confidence level (*Z*_*α*/2_ = 1.96), a power of 80% (*Z*_*β*_ = 0.84), an expected effect size of 0.19 (based on a 50% increase in team sports medicine practice), a standard deviation of 0.30, an intra-cluster correlation coefficient of *k* = 0.2, and 25 participants per cluster, the study estimates that it will need 12 clusters (teams) in both the control and intervention groups. Therefore, a total of 600 participants will be recruited, with 300 participants in each group. In summary, the study will recruit twelve (12) nurses and six (6) physiotherapists/doctors to supervise the intervention teams. The study will need 12 clusters (teams) in both the control and intervention groups, with a total of 600 participants (300 in each group) to detect a statistically significant change in team sports medicine practice at a 95% confidence level and 80% power, using the cluster randomized formula [38, 39].

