**Fig 2 pone.0278428.g002:**
[figure not shown]
FIFA football nurse recruitment strategy for participating teams in the Malawi Women’s Super league.

While medical resources required for football training and matches are known, most teams do not have medical support available to them either on a part-time or full-time basis. The 24 teams will be recruited and monitored for the 2022/2023 football season. The nurses will be approached through their District Health Officers (DHOs) while the teams will be approached through the country’s football governing body; Football Association of Malawi (FAM) and their specific District Sport Officers (DSOs) as is regulated in Malawi. A presentation on the trial will be made to the various DHOs, DSOs, and FAM by one of the investigators (EC), after which representatives from the teams will be invited to attend a presentation on the study protocol, where they will be invited to participate in the study in either the INT or CON group. The inclusion and exclusion criteria for the trial are as shown in **Table 2.**

**Table 2 pone.0278428.t002:** Inclusion and exclusion criteria for nurses, women’s football teams and physiotherapists/doctors for the FIFA football nurse trial.

Inclusion criteria	Exclusion criteria
Women’s football clubs in the Women’s League in Malawi registered with the Football Association of Malawi (FAM).	Women’s football clubs in the Women’s League in Malawi that already have medical personnel attached to their team.
Nurses registered with the Nurses and Midwives Council of Malawi with at least 3 years post graduate experience.	For potential supervisors, less than 3 years post qualification experience; incomplete FIFA Medical Diploma.
Physiotherapists with a recognised university qualification in physiotherapy, registered with the Medical and Dental Council of Malawi and with at least 3 years post graduate practice experience.	For potential Football Nurses, less than 3 years of post-qualification experience.
Medical doctors with a recognised university qualification (e.g., MBChB/MBBS) registered with the Medical and Dental Association of Malawi and at least 3 years post graduate practice experience.	For potential Football Nurses and supervisors, current attachment to a Women’s Football club in Malawi’s Women’s League
(for physiotherapists and medical doctors) Completion of the online FIFA Medical Diploma prior to the commencement of the project.	

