For the testing data such as injury risk (FMS, musculoskeletal screening), nutritional data (24h recall), and mental health assessment (SMHART-1), a mixed between-within-subjects ANOVA will compare the two arms over the whole intervention, then a post hoc Bonferroni test will be used to determine whether there are significant changes in the various scores and at what time point during the intervention these occur. Should there be a significant change in test scores, a one-way ANOVA will be performed at the specific time point to determine which specific test is different between arms. Additionally, a mixed effects logistic regression model will be used to examine the effects of arm assignment (intervention vs control) and time for categorical outcomes (e.g., sports injury prevention behaviours). To assess adherence and feasibility, descriptive statistics will be used to determine which aspects of the FIFA Football Nurse programme are best or worst implemented. Sensitivity analyses include adjustment for baseline team sports medicine practice and other potential confounding factors (e.g., previous injury, age, football experience, BMI, socioeconomic status). We will also include tests for effect-modification by relevant factors.

Additionally, data from the semi-structured interviews will be transcribed verbatim and a thematic analysis will be conducted using Braun and Clarke’s 6 step model [44] to group common themes and describe the experiences of women’s football stakeholders, and the barriers and facilitators towards the football nurse task-sharing approach. Analysis will be approached inductively by tagging meaning units which will then listed as themes, compared, and clustered to form categories, then assigned as general dimensions. Inter-rater reliability checks will be conducted by a blinded researcher, who will code a subset of the manuscripts and determine congruence of resulting themes. If clustering effects are observed in the data, these will be accounted for using appropriate statistical methods such as multilevel or hierarchical models.

All statistical tests conducted in this trial will be two-sided and p-values of < 0.05 will be considered statistically significant.

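### The printed formula and inputs give 11 teams per arm (550 participants), not 12 and 600; the error is conservative, but the team and participant counts need reconciling

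*Protocol article*

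**What the plan says.** **Sample size.** The section gives a cluster-trial formula with an added 1 and then its inputs. It starts from "Assuming a 95% confidence level" (1.96) and 80% power (0.84), and continues with "an expected effect size of 0.19 (based on a 50% increase in team sports medicine practice"), SD 0.30, intracluster correlation k = 0.2 and 25 participants per team. It concludes that "the study estimates that it will need 12 clusters (teams) in both the control and intervention groups", 300 participants per arm and 600 in total. The closing summary of the section repeats 12 and 600 as the numbers needed at 80% power. The data analysis text confirms the sidedness: "All statistical tests conducted in this trial will be two-sided and p-values of < 0.05 will be considered statistically significant".

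**Team size.** The descriptions of both arms, under Control or standard care and Football nurse intervention, state that "each team will have 30 registered players, one (1) team manager, and one (1) coach". The Recruitment section makes every player registered for 2022/2023 eligible, to be recruited through her team.

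**Team pool.** Recruitment describes a league of 24 teams, eight in each of three regions. Under Trial design the whole league "will be randomly assigned in a 1:1 ratio to either the Football Nurse intervention" or to control, by a draw within region after each team has agreed. Table 2 excludes clubs "that already have medical personnel attached to their team". The Recruitment text says that "most teams do not have medical support available to them either on a part-time or full-time basis", which leaves open that some do.

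**The concern.** The article shows the calculation in full and attributes 12 and 600 to it, so a reader can check the result, and it does not come out. The article commits to reporting under the CONSORT extension for cluster trials, so these figures will be carried into the results paper. As printed, a reader cannot tell whether 12 comes from the calculation, from an unstated allowance or simply from the size of the league. Nor can the reader see what margin remains if a team is ineligible or declines. The participant target has a similar problem: 25 per team and 30 per team stand in the same article with no sentence linking them.

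**Working it through.** **Inputs** (all from Sample size): 1.96; 0.84; difference 0.19; SD 0.30 in both arms; k = 0.2; m = 25.

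**Step 1. The plan's own formula.**
- (1.96 + 0.84)² = 7.84
- Sum of variances = 2 × 0.30² = 0.18
- Design effect = 1 + 24 × 0.2 = 5.8
- Denominator = 25 × 0.19² = 25 × 0.0361 = 0.9025
- C = 1 + 7.84 × 0.18 × 5.8 / 0.9025 = 1 + 9.07 = **10.07, i.e. 11 teams per arm**

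That is 22 teams and 22 × 25 = 550 participants (275 per arm), against the stated 24 teams and 600 (300 per arm). The stated 12 is not reproduced.

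**Step 2. What would give 12.** Each of these needs an input that the article does not state:

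| Changed input | C |
|---|---|
| 85% power | 11.39 |
| 10% loss, 10.07 / 0.90 | 11.19 |
| 15% loss, 10.07 / 0.85 | 11.85 |
| k = 0.23 to 0.25 | 11.20 to 11.95 |
| SD = 0.32 to 0.33 | 11.32 to 11.97 |

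Other readings of the effect size do not give 12. Taking 0.19 as a standardised difference gives 1 + 7.84 × 2 × 5.8 / 0.9025 = 101.8, i.e. 102 per arm. Taking 0.38 against 0.57 as proportions (0.19 / 0.5 = 0.38) gives 1 + 7.84 × 0.4807 × 5.8 / 0.9025 = 25.2, i.e. 26 per arm.

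**Step 3. Power by the same formula, solved for power.** Power = Φ(√[(C − 1) × 0.9025 / (0.18 × 5.8)] − 1.96).

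| Teams per arm | Power |
|---|---|
| 12 | Φ(3.084 − 1.96) = 86.9% |
| 11 | Φ(2.940 − 1.96) = 83.7% |
| 10 | Φ(2.789 − 1.96) = 79.7% |

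A t-test on team means gives nearly the same values: 86.8%, 83.5% and 79.4%.

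**Step 4. Participants.** 24 × 25 = 600, but 24 × 30 = 720 players, or 24 × 32 = 768 people with manager and coach. The effect on the number of teams is slight. With m = 30 the design effect is 6.8 and C = 1 + 7.84 × 0.18 × 6.8 / 1.083 = 9.86, i.e. 10 per arm.

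**Step 5. Teams.** The league has 3 × 8 = 24 teams, and the stated requirement is 2 × 12 = 24. No team is spare against that requirement, while Table 2 can remove teams and each team must agree before the draw.

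**The case against.** The best defence is that nothing in the design needs to change. Twelve exceeds 11, and it suits the league: four teams per arm in each of three regions, which 11 cannot match evenly. A 10–15% allowance would also lead to 12, and a condensed article may leave such an allowance to the full protocol. All this is fair as to consequence. But the article gives neither reason. It presents 12 as the output of the printed inputs at 80% power, and that statement is wrong.

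On participants, 30 is squad registration and 25 may be expected participation, since individual consent or assent is required and taking part is voluntary. That is plausible, so the gap is an unexplained assumption and not proof of a wrong target.

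A reader might draw three stronger conclusions, which the document does not support:

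- **That the trial is underpowered.** On the printed inputs it has more than 80% power.
- **That it fails unless all 24 teams take part.** This pulls against the finding that 11 per arm is enough. Losing one team per arm leaves 83.7%, and at 10 per arm power is 79.7%, essentially 80%. The article also gives no count of ineligible teams. What stands is the wording conflict between randomising the whole league and excluding some clubs.
- **That 87% can be quoted as the trial's power without qualification.** It holds only if about 25 individual scores per team feed the outcome. The primary outcome section says that practice is evaluated at team level, whereas the data analysis text takes a mean and SD within each team, which suggests individual scores. If there were a single score per team with SD 0.30, the formula with m = 1 would give 1 + 7.84 × 0.18 / 0.0361 = 40.1, i.e. 41 teams per arm, and power at 12 of Φ(√[11 × 0.0361 / 0.18] − 1.96) = about 32%. The article does not settle this, so neither figure should be stated as fact.

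**Conclusion.** The point holds as an arithmetic and consistency error of limited consequence. The printed calculation gives 10.07, i.e. 11 teams per arm and 550 participants. The stated 12 and 600 are about 9% higher (12 / 11 = 600 / 550 = 1.09). The error is conservative: 12 per arm corresponds to 86.9% power, not 80%, given individual scores with SD 0.30, k = 0.2, 25 per team and a true difference of 0.19. The 25 per team is not reconciled with 30 eligible registered players (600 against 720). Randomising every team in the league conflicts with the Table 2 exclusion. Neither of these last two threatens the trial, but both leave the reader unsure who and how many will be recruited.

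**What to change.** Reword the sample size paragraph and one sentence under Trial design:

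1. State that the formula gives 10.07, i.e. 11 teams per arm, and that 12 per arm is used because all eligible league teams are randomised. If a loss allowance was applied instead, state it.
2. If power is quoted, use the formula throughout (86.9% at 12 per arm, 83.7% at 11, 79.7% at 10). Say that it assumes about 25 individual scores per team, SD 0.30 and intracluster correlation 0.2.
3. Either give 25 of 30 registered players as the assumed participation, or replace 25 and 600 with the number to be recruited and rerun the formula.
4. Under Trial design, replace the whole league with all eligible, consenting teams, drawn within region as already planned.

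The cost is a few sentences. The design and the number of teams approached stay the same.
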